# Fluoxetine for motor recovery after acute intracerebral hemorrhage (FMRICH): study protocol for a randomized, double-blind, placebo-controlled, multicenter trial

**DOI:** 10.1186/1745-6215-14-77

**Published:** 2013-03-19

**Keywords:** Intracerebral hemorrhage, Stroke, Motor recovery, Fluoxetine, Randomized controlled trial

## Abstract

**Background:**

Spontaneous, nontraumatic intracerebral hemorrhage (ICH) is a subtype of stroke that causes a great amount of disability and economic and social burden. This is particularly true in developing countries where it accounts for between 20% and 50% of all strokes. Pharmacological and surgical interventions have been attempted to reduce the mortality and disability caused by ICH, with unsuccessful results. Recently, the use of fluoxetine in addition to physical rehabilitation has been proven useful to improve motor recovery following cerebral infarct. The purpose of this study is to test whether a 3-month treatment with fluoxetine enhances motor recovery in nondepressed patients with acute intracerebral hemorrhage.

**Methods/design:**

Our study is a randomized, double-blind, placebo-controlled, multicenter clinical trial. We will recruit 86 patients with intracerebral hemorrhage of both sexes, aged >18 years, from four Mexican hospitals. The patients will receive either 20 mg of fluoxetine or a placebo once daily for 90 days. The primary outcome is the mean change in the Fugl-Meyer Motor Scale score between inclusion (day 0) and day 90. The secondary outcomes will be changes in the Barthel Index, the Modified Rankin scale and the National Institutes of Health stroke scale. The outcomes will be measured at day 42 ± 7days and at day 90, for a total of four visits with each subject (at screening and at 0, 42 and 90 days).

**Discussion:**

Current guidelines recommend early supported hospital discharge and home-based rehabilitation programs as the only cost-effective intervention to aid the recovery of patients with intracerebral hemorrhage. Nevertheless, such interventions are dependent on available resources and funding, which make them very difficult to implement in developing countries. We believe that the identification of a helpful pharmacological intervention to aid the motor recovery of these patients will constitute a breakthrough that will have a major impact in reducing the burden of disease caused by this subtype of stroke worldwide, especially in the developing world.

**Trial registration:**

Current Controlled Trials NCT01737541

## Background

Spontaneous, nontraumatic intracerebral hemorrhage (ICH) is a significant cause of morbidity and mortality worldwide, and no treatment has been proven effective [1]. Each year, approximately 1 million people suffer from ICH [2], which causes a great amount of disability and economic and social burden. This is particularly true in developing countries where ICH accounts for between 20% and 50% of all strokes [3]. Hispanic Americans and especially Mexican Americans have been shown to have an increased risk of ICH compared with non-Hispanic whites [4]. The higher prevalence of ICH appears to be very similar in Hispanic patients living in Mexico and in the USA [5]. Despite these data, it is not clear whether this excess in incidence is due to differences inherent to ethnicity, or due to other differences in the disease pathogenesis.

Several therapeutic approaches have been attempted to reduce the burden in terms of death and disability from ICH, including pharmacological and surgical interventions, but trials have been largely unsuccessful [6]. These failures have encouraged a focus on management in intensive care units and physical rehabilitation as the mainstream approaches to reduce mortality and disability, respectively [7].

Recently, the use of antidepressant drugs as an adjunctive treatment to augment recovery in stroke patients has been studied in small clinical trials [8-11]. In 2011, Chollet and colleagues [12] tested adjunctive treatment with fluoxetine in addition to physical rehabilitation to improve motor recovery from cerebral infarct (CI), with excellent results. Subsequent evidence indicated that this improvement is persistent through time [13].

It is thus necessary to elucidate the relative importance and potential benefits of the use of fluoxetine in ICH patients, so that this drug can play a role as an adjunctive therapy to aid the motor recovery of ICH patients, similar to CI patients.

This study will be the first reported randomized, double-blind, placebo-controlled clinical trial of the use of fluoxetine for motor recovery in patients with ICH. The main purpose of this study is to test whether a three-month treatment with fluoxetine enhances motor recovery in nondepressed patients with acute intracerebral hemorrhage.

## Methods/design

### Objectives and hypothesis

#### Objectives

The main objectives of this trial are to (1) compare the magnitude of motor recovery, measured with the Fugl-Meyer Motor Scale (FMMS), in patients receiving fluoxetine with that of patients receiving placebo, and (2) establish the relationship between motor recovery and functional recovery as measured with the Barthel index (BI), the modified Rankin scale and the National Institutes of Health stroke scale (NIHSS).

#### Hypothesis

We hypothesize that the mean change in FMMS between inclusion (day 0) and day 90 will be significantly higher in the patients receiving fluoxetine compared with those receiving placebo.

#### Study design and period

This study is a 12-week randomized, double-blind, placebo-controlled, multicenter trial at four Mexican hospitals. Figure 1 shows the schematic flow of the study.

**Figure 1 F1:**
[figure not shown]
Flowchart of the fluoxetine for motor recovery after acute intracerebral hemorrhage (FMRICH) clinical trial.

#### Study groups

The study will include the following two arms: the fluoxetine group (treatment arm) and the placebo group (control arm).

### Population

The subjects will be patients of both sexes with acute ICH and ages above 18 years.

#### Eligibility criteria

Inclusion Criteria

1. Men and women ages ≥ 18 years

2. Individuals who meet one of the following criteria:

2.1.  Patients who had an acute intracerebral hemorrhage within the past 10 days causing hemiparesis or hemiplegia

2.2.  Fugl-Meyer motor scale (FMMS) scores ≤ 55

3. Written, informed consent for participation in the trial

Exclusion Criteria

1. Severe post-stroke disability (National Institutes of Health stroke scale [NIHSS] score >20)

2. Premorbid disability, evidenced by residual motor deficit from a previous stroke

3. Comprehension deficits or severe aphasia

4. Previous diagnosis of depression or one of the following:

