#### Sample size calculation

A sample size of 35 in each group will be sufficient to detect a clinically important difference of 14.5 points on the FMMS, assuming a standard deviation of 21.3 FMMS points on the basis of the findings of the fluoxetine in motor recovery of patients with acute ischaemic stroke (FLAME) trial [12], using a two tailed *t*-test of the difference between means, a power of 80%, and a significance level of 5%. This number has been increased to 44 per group (total of 88), to allow for a predicted 20% loss to follow-up.

The formula for the sample size for comparison of two means (two-sided) is as follows:

$$n=\frac{2\sigma^{2}{\left(Z_{a}+Z_{b}\right)}^{2}}{\delta^{2}}$$

$$Z_{a}=1.96$$

$$Z_{b}=0.84$$

δ = size of difference of clinical importance = 14.5

σ = standard deviation of the primary outcome variable = 21.3

$$n=\frac{2*21.3^{2}{\left(1.96+0.84\right)}^{2}}{14.5^{2}}\approx 35$$

Adjusted for 20% patients lost to follow-up:

$$n_{c}=\frac{n}{1-l}\approx 44$$

*l* = expected frequency of patients lost to follow-up = 0.20

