#### Study schedule

The measurements that will be carried out at each visit are listed in Table 1.

**Table 1 T1:** Study schedule of fluoxetine for motor recovery after acute intracerebral hemorrhage (FMRICH) clinical trial

	**Screening**	**Visit 1**	**Visit 2**	**Visit 3**
Informed consent	•			
Inclusion criteria	•			
Demographics^a^	•			
Inclusion/exclusion criteria check	•			
Vital signs^b^		•	•	•
Medical/drug use history^c^		•		
Smoking/drinking status		•		
Laboratory tests^d^		•		
Lipid test^e^		•		
Coagulation tests^f^		•		•
Date of bleeding		•		
Condition associated with bleeding^g^		•		
BCT	•			
Date of BCT	•			
Volume of the hemorrhage^h^	•			
Localization of the hemorrhage	•			
Concomitant medication	•	•	•	•
Adverse event			•	•
NHISS		•	•	•
Depression Scale	•		•	•
Fugl-Meyer Motor Scale	•		•	•
Patient’s rehabilitation log			•	•
Barthel Index		•	•	•
Modified Rankin Scale		•	•	•
Pill count			•	•

^a^Age, gender, educational level, marital status, occupational status, date of birth, contact address and telephone number. ^b^Blood pressure (mmHg), pulse (beats/minute) and body temperature (°C). ^c^Diabetes Mellitus, hypertension, dyslipidemia. ^d^Hemoglobin, hematocrit, red blood cell count, white blood cell count, platelet count, blood urea, nitrogen/creatinine ratio, fasting plasma glucose. ^e^Total cholesterol (mg/dl), high-density lipoprotein cholesterol (mg/dl), low-density lipoprotein cholesterol (mg/dl), very low-density lipoprotein cholesterol (mg/dl), triglyceride (mg/dl). ^f^International Normalized Ratio, prothrombin time, activated partial thromboplastic time. ^g^Trauma, Drugs, bleeding disorder, exercise. ^h^ABC/2 method. BCT, Brain Computed Tomography; NIHSS, National Institutes of Health Stroke Scale.

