### Primary outcome

The primary outcome is the mean change in FMMS score between inclusion (day 0) and day 90.

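### Inclusion criterion 2 joins acute ICH with hemiparesis and FMMS ≤ 55 by OR, which contradicts the stated population and leaves the FMMS threshold without effect in it

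*Protocol article*

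**What the plan says.** All references are to the protocol article.

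- **Population** sets the target: "The subjects will be patients of both sexes with acute ICH and ages above 18 years".
- **Eligibility criteria**, inclusion criterion 2, opens with "Individuals who meet one of the following criteria" and lists two items. Item 2.1 is "Patients who had an acute intracerebral hemorrhage within the past 10 days causing hemiparesis or hemiplegia". Item 2.2 is "Fugl-Meyer motor scale (FMMS) scores ≤ 55".
- The other two inclusion criteria concern age and written consent. Among the exclusions, the only limit on the severity of the current stroke is "Severe post-stroke disability (National Institutes of Health stroke scale [NIHSS] score >20".
- **Primary outcome** uses the same scale as item 2.2: "The primary outcome is the mean change in FMMS score between inclusion (day 0) and day 90".
- **Sample size calculation** plans to "detect a clinically important difference of 14.5 points on the FMMS" with an SD of 21.3.

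**The concern.** The connecting phrase makes 2.1 and 2.2 alternatives, so either one satisfies criterion 2. The diagnosis, the 10-day window and the motor deficit sit only in 2.1, and the FMMS limit sits only in 2.2. Each item can be bypassed by meeting the other.

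Two things are at stake. First, the operative list does not define the population that the title, the objectives and the Population section describe. Second, the trial fixes a baseline limit on its own primary outcome scale and then words it so that it does not bind. Four hospitals recruit. One that follows the list literally will enrol ICH patients above 55, while one that assumes both items are needed will not. Detection of an eligibility violation is also the first withdrawal criterion, so the same uncertainty extends to which randomized patients count as violations.

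**Working it through.** **Step 1. Who passes criterion 2?** The two items give four combinations.

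| 2.1 met (ICH within 10 days, with hemiparesis or hemiplegia) | 2.2 met (FMMS ≤ 55) | As written (either) | If both required | Agrees with Population section? |
|---|---|---|---|---|
| yes | yes | passes | passes | yes |
| yes | no | passes | fails | yes: acute ICH, but FMMS above 55 |
| no | yes | passes | fails | not assured: may have no ICH, or an older bleed |
| no | no | fails | fails | – |

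The two readings differ in rows 2 and 3.

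**Step 2. Does another rule close row 3 (2.2 without 2.1)?** No other inclusion or exclusion item names ICH or a time window. The Population section does require acute ICH, so it conflicts with the list. It does not state the 10-day window.

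**Step 3. Does another rule close row 2 (2.1 without 2.2)?** No. These patients do have acute ICH, so the Population section admits them. The NIHSS limit removes severe strokes and leaves mild ones in. Nothing else caps baseline FMMS. For every patient who meets 2.1, the result of 2.2 makes no difference.

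**Step 4. Could the phrase be meant as both?** The same construction introduces the depression items in exclusion 4 (a HAD score threshold, or recent antidepressant use), where alternatives are clearly meant. A site has no textual reason to read it differently in criterion 2.

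**Step 5. Is a planned figure wrong?** Inputs from Sample size calculation: δ = 14.5, σ = 21.3, two-sided 5%, power 80%, loss 20%.

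- Article's formula: 2 × 21.3² × (1.96 + 0.84)² / 14.5² = 33.8. The exact two-sample t-test gives 34.9, so 35 per group.
- Loss to follow-up: 35 / (1 − 0.20) = 43.75, so 44 per group.

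The stated figures reproduce, and the wording defect does not touch this arithmetic.

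**Step 6. Hypothetical effect on power.** Assume a share f of analysed patients shows no treatment effect at all, and the SD stays at 21.3. The mean difference becomes 14.5 × (1 − f). Two-sample t-test power:

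| f (assumed) | Mean difference | Power, 35 per group | Power, 44 per group |
|---|---|---|---|
| 0% | 14.5 | 0.80 | 0.88 |
| 10% | 13.05 | 0.71 | 0.81 |
| 20% | 11.6 | 0.61 | 0.71 |
| 30% | 10.15 | 0.50 | 0.60 |

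The 44 column is shown because Statistical analysis puts all randomized subjects in the full analysis set and fills missing outcomes by LOCF. The article supplies no value for f, so the table shows sensitivity to an assumption. It does not measure this defect.

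**The case against.** The strongest reply is that this is an obvious slip that no site would act on. The Population section stands just above the list and requires acute ICH. Patients are recruited in emergency departments, and Table 1 places brain CT, hemorrhage volume and hemorrhage location at Screening. This largely stands for row 3: a reader might infer that the trial will in practice randomize patients with infarct, and the article does not support that. The reply does not reach row 2, because none of those safeguards concerns FMMS.

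Three stronger readings are also tempting and should not be drawn.

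- *Patients with nearly full motor scores will enter.* The article does not give the FMMS maximum, and 2.1 still demands hemiparesis or hemiplegia. The supportable statement is any FMMS above 55.
- *The trial loses a known amount of power.* The shares in Step 6 are assumed. The 14.5 points are a difference between group means and not a gain that each patient must make, so a patient with less room on the scale is not thereby a patient with zero effect. A subgroup with little room would probably also change the SD. At 44 per group, a 10% share would still leave power just above 80%.
- *Traumatic bleeds are eligible*, because Table 1 lists "Trauma, Drugs, bleeding disorder, exercise" among associated conditions recorded at Visit 1. The abstract and Background introduce ICH as spontaneous and nontraumatic, and that meaning carries into later uses of the abbreviation. Recording a condition does not show that it is admitted.

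It is also fair to say that the article nowhere states that both items were intended; that is an inference. Condensation for a journal does not explain the problem, however, since the connector is stated and not left out.

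**Conclusion.** The concern holds as an error of wording and an internal contradiction. As written, criterion 2 admits through 2.2 alone patients whom the Population section excludes, and through 2.1 alone ICH patients at any FMMS above 55. The first is unlikely to happen in practice. The second is not blocked anywhere, and it matters more because FMMS is both the entry threshold and the primary endpoint.

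The size cannot be stated from the article. How many patients fall in row 2 is unknown, and the power figures are illustrations only. The case for correction rests on the text: an operative eligibility rule disagrees with the stated population and makes its own threshold idle. It should be corrected even if no patient has yet entered through the gap.

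**What to change.** Reconcile the Population section with inclusion criterion 2 by replacing the opening of criterion 2 with wording that requires both 2.1 and 2.2. This reading agrees with the Population section and gives the FMMS threshold a function. Because the intention is inferred, the sponsor should confirm it in the amendment.

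Notify the four sites of the corrected wording. Check every patient enrolled since November 2012 against it, and record how many met only one of the two items. Those patients remain in the full analysis set, which the article defines as all randomized subjects.

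The cost is a one-line amendment, a site notice and a check of existing records. No new measurement is needed, since Table 1 already schedules both brain CT and FMMS at Screening. If some sites have been enrolling patients above 55, recruitment may slow; the article gives no figure from which to estimate by how much.

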4.1.  Hospital anxiety and depression scale (HAD) score ≥11 points

4.2.  Taking antidepressant drugs two weeks before inclusion

5. Taking neuroleptic drugs or benzodiazepines 2 weeks before inclusion

6. Other major diseases with life expectancy ≤ 3 months.

Withdrawal Criteria

1. Detection of eligibility violations

2. Poor compliance (<90%) or noncompliance

3. Use of any medication or treatment during the trial that could affect the study results

4. Occurrence of a serious adverse event

4.1. Subject has an acute reaction (allergy, shock) to the investigational product

4.2. Subject develops depression, evidenced by HAD score ≥11 points at Visit 2

5. Subject withdraws consent or is uncooperative

The patients withdrawn after randomization will be followed for outcomes

#### Interventions

Participating subjects assigned to either the treatment group or the placebo group will be instructed to take a pill of fluoxetine (20 mg) or placebo once daily for 90 days. Fluoxetine and placebo tablets will be identical in form, color, odor and packaging.

#### Concomitant treatments and forbidden drugs

The product name, use, dosage and duration of all medications used by the patients during their hospital stay and follow-up will be recorded. Only the use of antidepressants will be prohibited.

#### Sample size calculation

A sample size of 35 in each group will be sufficient to detect a clinically important difference of 14.5 points on the FMMS, assuming a standard deviation of 21.3 FMMS points on the basis of the findings of the fluoxetine in motor recovery of patients with acute ischaemic stroke (FLAME) trial [12], using a two tailed *t*-test of the difference between means, a power of 80%, and a significance level of 5%. This number has been increased to 44 per group (total of 88), to allow for a predicted 20% loss to follow-up.

The formula for the sample size for comparison of two means (two-sided) is as follows:

$$n=\frac{2\sigma^{2}{\left(Z_{a}+Z_{b}\right)}^{2}}{\delta^{2}}$$

$$Z_{a}=1.96$$

$$Z_{b}=0.84$$

δ = size of difference of clinical importance = 14.5

σ = standard deviation of the primary outcome variable = 21.3

$$n=\frac{2*21.3^{2}{\left(1.96+0.84\right)}^{2}}{14.5^{2}}\approx 35$$

Adjusted for 20% patients lost to follow-up:

$$n_{c}=\frac{n}{1-l}\approx 44$$

*l* = expected frequency of patients lost to follow-up = 0.20

#### Randomization method

A pharmaceutical laboratory (Psicofarma™ S.A. de C.V.) will be responsible for the manufacture and randomization of the investigational product, which will be achieved using a web-based randomization program. This program will be set to assign participants equally to each site at a ratio of 1:1.

Each of the sites will be assigned 22 participants. The manufacturer will then deliver the pre-randomized bottles containing the investigational product to each recruiting center.

Study subjects who satisfy the eligibility criteria at each recruiting center will receive the investigational product corresponding to a consecutive number assigned according to their entrance to the study.

#### Blinding

Both the investigator and the subject will be blinded to the assignment of the study drugs. The manufacturer of the tablets will label the investigational drugs by the randomization code number. The labeled experimental products will be provided to the recruiting centers by the manufacturer. An envelope containing all randomization codes will be delivered to the principal investigator and will be kept sealed until the conclusion of the trial.

### Recruitment

Participants will be recruited at the emergency departments at four Mexican hospitals:

The Centenario Hospital ‘Miguel Hidalgo’ (located in Aguascalientes, a midsized city in central México), the Instituto Nacional de Neurología y Neurocirugía (located in Mexico City), the Antiguo Hospital Civil de Guadalajara ‘Fray Antonio Alcalde’ (located in Guadalajara, a major city in western Mexico) and the Hospital Regional de Alta Especialidad ‘[name] Casassus’ (located in Villahermosa, a midsized city in the south of Mexico).

#### Study schedule

The measurements that will be carried out at each visit are listed in Table 1.

**Table 1 T1:** Study schedule of fluoxetine for motor recovery after acute intracerebral hemorrhage (FMRICH) clinical trial

	**Screening**	**Visit 1**	**Visit 2**	**Visit 3**
Informed consent	•			
Inclusion criteria	•			
Demographics^a^	•			
Inclusion/exclusion criteria check	•			
Vital signs^b^		•	•	•
Medical/drug use history^c^		•		
Smoking/drinking status		•		
Laboratory tests^d^		•		
Lipid test^e^		•		
Coagulation tests^f^		•		•
Date of bleeding		•		
Condition associated with bleeding^g^		•		
BCT	•			
Date of BCT	•			
Volume of the hemorrhage^h^	•			
Localization of the hemorrhage	•			
Concomitant medication	•	•	•	•
Adverse event			•	•
NHISS		•	•	•
Depression Scale	•		•	•
Fugl-Meyer Motor Scale	•		•	•
Patient’s rehabilitation log			•	•
Barthel Index		•	•	•
Modified Rankin Scale		•	•	•
Pill count			•	•

^a^Age, gender, educational level, marital status, occupational status, date of birth, contact address and telephone number. ^b^Blood pressure (mmHg), pulse (beats/minute) and body temperature (°C). ^c^Diabetes Mellitus, hypertension, dyslipidemia. ^d^Hemoglobin, hematocrit, red blood cell count, white blood cell count, platelet count, blood urea, nitrogen/creatinine ratio, fasting plasma glucose. ^e^Total cholesterol (mg/dl), high-density lipoprotein cholesterol (mg/dl), low-density lipoprotein cholesterol (mg/dl), very low-density lipoprotein cholesterol (mg/dl), triglyceride (mg/dl). ^f^International Normalized Ratio, prothrombin time, activated partial thromboplastic time. ^g^Trauma, Drugs, bleeding disorder, exercise. ^h^ABC/2 method. BCT, Brain Computed Tomography; NIHSS, National Institutes of Health Stroke Scale.

### Measurement tools

#### Questionnaires

##### The fugl-meyer assessment (FMA)

The Fugl-Meyer assessment (FMA) [14] is a stroke-specific, performance-based impairment index. It is designed to assess motor functioning, balance, sensation and joint functioning in hemiplegic post-stroke patients. Each of the five FMA domains can be separated to test a specific construct. The motor domain (FMMS) includes items assessing movement, coordination and reflex action of the shoulder, elbow, forearm, wrist, hand, hip, knee, and ankle. We will use the FMMS to assess the motor recuperation of patients in this study.

